## Abstract

**Background:** Regarding the strong auditory spatial plasticity capability of the central auditory system and the effect of short-term and long-term rehabilitation programs in elderly people, it seems that an auditory spatial training can help this population in informational masking release and better track speech in noisy environments. The main purposes of this study are developing an informational masking measurement test and an auditory spatial training program.

**Protocol:** This study will be conducted in two parts. Part 1: develop and determine the validity of an informational masking measurement test by recruiting two groups of young (n=50) and old (n=50) participants with normal hearing who have no difficulty in understanding speech in noisy environments. Part 2 (clinical trial): two groups of 60-75-year-olds with normal hearing, who complain about difficulty in speech perception in noisy environments, will participate as control and intervention groups to examine the effect of auditory spatial training. Intervention: 15 sessions of auditory spatial training. The informational masking measurement test and Speech, Spatial and Qualities of Hearing Scale will be compared before intervention, immediately after intervention, and five weeks after intervention between the two groups.

**Discussion:** Since auditory training programs do not deal with informational masking release, an auditory spatial training will be designed, aiming to improve hearing in noisy environments for elderly populations.

**Trial registration:** Iranian Registry of Clinical Trials (
IRCT20190118042404N1) on 25
^th^ February 2019.

## Introduction

Many older adults complain about speech perception in noisy situations. It is clear that poorer speech recognition in the elderly population can occur due to various factors, including peripheral hearing impairment or decline in cognitive capabilities and processing defects at supra threshold levels. It is difficult to determine the exact role of each of these factors in developing speech problems in the elderly
^1^. Most elderly individuals complain about the difficulty in understanding speech in noisy environments, despite having normal hearing thresholds
^2^. The spectro-temporal overlap between target and competing speech, which leads to poor target identification, is called energetic masking
^3^. Energetic masking is caused by physical interactions between target and competing speech
^4,
5^ at the low level of the peripheral auditory system
^6^. Recent research has suggested that when competing signals occur randomly or when there is a high similarity between target and competing signals (for example, when both signals are speech), another type of masking occurs. This type of masking, which occurs in response to uncertainty of the competing signal or similarity between target and competing signals, is called non-energetic or informational masking
^7,
8^. It leads to failure in selecting auditory objects and therefore impairs auditory scene analysis. Generally, in contrast with the energetic masking, which occurs due to the limitations caused by frequency selectivity at peripheral levels, informational masking reflects the processing capacity limitations at central auditory levels
^9^. So, the type of background noise heavily influences the extent of the damage imposed to speech intelligibility
^1^. Generally, hearing problems worsen in noisy environments when the target speech is covered by a competing signal. In this situation, in addition to energetic masking, informational masking also occurs
^10^.

Various studies have indicated that with an increase in age, side-effects of competing noises will increase
^1,
10–
12^. Different studies have revealed that elderly populations, who do not have peripheral auditory impairment, suffer from diminished ability of using acoustic and phonetic signs to separate speech from background noise, compared to young people; therefore, more informational masking occurs in this population
^10,
13^. Since problems with understanding speech will reduce social interactions of the elderly population, it is very important to develop effective auditory rehabilitation programs to prevent their isolation and to improve their quality of life
^1^.

Auditory spatial processing plays an important role in speech recognition in complex noisy environments
^14^, since it enables the listener to differentiate the target signal from competing signals via auditory scene analysis and forming auditory streams
^15^. Based on the results of different studies, it has become clear that the most important sign of informational masking release is spatial separation of target and competing signals
^16–
18^. In addition, it has been shown that auditory spatial processing ability is lower in the elderly with normal hearing than in young people. The reduction of localization accuracy and taking advantage of auditory spatial processing, consequently decreasing binaural processing, are not totally related to impaired hearing thresholds
^19,
20^. Hence, it leads to poorer speech recognition in elderly people with normal hearing in noisy environments
^14^. On the other hand, it has been shown that the elderly population need a higher signal to noise ratio for speech recognition in the presence of noise, compared to young people
^11,
21^. These changes are possibly due to the reduction in the ability of using acoustic and phonetic signs to separate target signals from background noise
^11^. Therefore, in elderly people, without considering the peripheral hearing impairment, the ability to use spatial and non-spatial signs for informational masking release diminishes due to the reduction of cognitive processing abilities
^11,
12^, temporal processing defects
^10^, defects in the connection between hemispheres, and diminished ability to separate simultaneous sounds
^11^.

Current neuroscientific studies have suggested that the central auditory system has a strong neuroplasticity capability for auditory spatial processing
^22,
23^ and since the effect of short-term and long-term auditory rehabilitation programs has been demonstrated in elderly people
^2^, it seems that by providing auditory spatial training, we can aid the elderly population to perform informational masking release, preventing them from missing conversations in noisy environments.

The present study has two parts. The first part of this research will be conducted to develop a test for measuring and evaluating the informational masking. Between different researches on informational masking, coordinate response measure (CRM) sentences appear to be a good option to differentiate between energetic and informational masking
^24^. By using these phrases as the target and competing signals, a high semantic and syntactic similarity occurs, which is an important factor in introducing informational masking
^25^. Therefore, since the Persian version of these sentences are not available, we will prepare them and after that, we will develop a new informational measurement test. The second part of this research will be a clinical trial of an auditory spatial training program in elderly people with normal hearing, which would diminish informational masking. The main hypothesis for the second part of the study is that presenting an auditory spatial training for elderly people would be effective in the improvement of speech recognition in noisy environments by stimulating the centers related to binaural processing.

## Protocol

This is version 2 of this protocol.

### Study design, setting and participants

This research will be conducted in the Audiology Clinic of Rehabilitation School of Iran University of Medical Sciences.

This study consists of two main parts. Part 1: develop and determine an informational masking measurement test and explain its validity characteristics in a test development study, conducted cross-sectionally. The study population will be a group of elderly (60 to 75 years old) and a group of young (20 to 40 years old) people. The young people will be recruited from rehabilitation students of Iran University of Medical Sciences, while elderly people are those referred to the audiology clinics of Iran University of Medical Sciences.

Part 2 (simple randomized clinical trial): the effect of training on informational masking release. This part of study is a simple randomized clinical trial design and patients will be randomly assigned into two groups of control (not receiving auditory spatial training) and intervention (receiving auditory spatial training). The random allocation will be performed based on balanced randomization [1:1] where the allocation will be applied by random number table (those assigned an odd number, control group; those assigned an even number, intervention group). This allocation sequence will be generated by one of the audiology clinic staff of the IUMS who will not have any role in the study. An elderly population, 60–75-years-old, who are referred to the audiology clinics of Iran University of Medical Sciences will be selected. The two groups will be matched for age and gender. Those in the control group will not receive any rehabilitation programs during the study.

*Inclusion criteria (for all participants in the study):* auditory thresholds ≤25dB within the 250–8000Hz frequency range for ensuring the normal pure tone audiogram or normal peripheral hearing, ensuring lack of salient cognitive problems using Mini Mental State Examination (MMSE)
^26^; having diploma or higher degree; right-handedness (using Edinburgh handedness inventory); speaking Farsi and being monolingual; complaint about speech in noise perception difficulties (just for those in part 2 of the study); and normal condition of middle ear function.

*Exclusion criteria (for all participants in the study):* unwillingness for participation in each step of research and not meeting inclusion criteria.

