### Sample size

***Part 1.*** The study of Terwee
*et al.* was considered as the basic study to determine the sample size of the first part of our study. They suggested that at least 50 patients in each group must be included to evaluate the construct validity
^43^. In total, 50 young people aged between 20 and 40 years and 50 elderly people aged between 60 and 75 years, with normal peripheral hearing who do not suffer from speech understanding in noisy environments, will be recruited.

***Part 2.*** The following formula is used to determine the sample size:

$$\text{n}=\frac{{\left(Z_{1-\alpha /2}+Z_{1-\beta }\right)}^{2}\left({S_{1}}^{2}+{S_{2}}^{2}\right)}{\left(\mu_{1}-\mu_{2}\right)}$$

n= (Z1−α/2+Z1−β)2(S12+S22)(μ1−μ2)

S
_1_: standard deviation of the studied variable in the first group (case, exposed, or intervened)

S
_2_: standard deviation of the studied variable in the second group (control, unexposed, or compared)

µ
_1_: mean of the studied variable in the first group

µ
_2_: mean of the studied variable in the second group

α=0.05

β=80%

Z= 1.96

In this formula, the studied variable is the extent of informational masking changes before and after the intervention. There is no previous study, which was used the same training as this study proposes; therefore, we considered the study of Delphi
*et al.* which was on a group of elderly individuals
^44^. In her study the mean and standard deviation of the improvement in the main variable were 37.5 and 25.17 in the experimental group and 25.17 and 18.15 in the control group, respectively. According to this, the sample size calculated 14 in each group. By assuming 20% drop out, so we will use 18 people in each group.

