### Study status

The study started in December 2018 and will continue until December 2019. To date, the enrolment of the patients has been performed and the allocation will be performed in the near future.

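### The odd/even allocation rule does not guarantee the equal, age- and gender-matched groups that the protocol promises

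*Protocol article*

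**What the plan says.** The protocol's section on study design, setting and participants makes four statements about allocation in Part 2.

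- The type: "This part of study is a simple randomized clinical trial design".
- The ratio and tool: "The random allocation will be performed based on balanced randomization [1:1] where the allocation will be applied by random number table".
- The rule: "those assigned an odd number, control group; those assigned an even number, intervention group". The sequence is generated by a clinic staff member who has no role in the study.
- The promised result: "The two groups will be matched for age and gender".

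The sample size section adds fixed group sizes: "By assuming 20% drop out, so we will use 18 people in each group". The study status section gives the timing: "the enrolment of the patients has been performed and the allocation will be performed in the near future".

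The allocation description includes no blocking, stratification, minimisation or pairing.

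**The concern.** The article does not leave the mechanism to a fuller document. It names one, and then states properties that this mechanism does not secure. Parity of a random number, applied person by person, is unrestricted randomisation. It gives an equal chance of each arm, but it controls neither the final group sizes nor the mix of age and gender.

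Two things are at stake. The first is precision: in a trial of 36 people, chance differences in age or gender between arms can be sizeable. The second matters more. Because enrolment precedes allocation, everyone's age and gender can be known when the draw is made. If the draw gives visibly unmatched groups, the protocol contains a promise that the draw has not met, and no rule for what happens next. Redrawing until the groups look alike, or moving individuals, would make allocation depend on someone's choice. A reader could not tell from the text whether that had happened.

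**Working it through.** **Inputs.** Planned total 2 × 18 = 36 (Sample size). Probability 1/2 for each arm, independently for each person (the natural reading of simple randomisation by odd or even number). The protocol gives neither the number of women nor the SD of age, so those are assumptions with ranges below. It also does not state the number actually enrolled; 36 is assumed.

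**The plan's own group size.** The step from 14 to 18 reproduces: 14 / (1 − 0.20) = 17.5, rounded up to 18. The 14 itself does not follow from the stated inputs. With the difference squared in the denominator, as the standard formula requires, 7.849 × (25.17² + 18.15²) / (37.5 − 25.17)² = 7.849 × 962.95 / 152.03 = 49.7. That is a separate sample-size matter; this check uses only the planned 36.

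**Group sizes.** The number in one arm is Binomial(36, 0.5).
- P(exactly 18:18) = C(36,18) / 2³⁶ = 9,075,135,300 / 68,719,476,736 = 0.132.
- P(22:14 or worse, either direction) = 0.243.
- P(one arm with 13 or fewer) = 0.132.

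**Cost of unequal size alone.** Effective size per arm = 2·n₁·n₂/36.
- 14:22 gives 2 × 14 × 22 / 36 = 17.1.
- 13:23 gives 2 × 13 × 23 / 36 = 16.6.

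Both compare with 18 for an even split, so the loss is small.

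**Gender.** Under the odd/even rule, the women and the men divide as two independent binomials with probability 1/2. Summing over all divisions, the probability that the share of women differs between arms by at least 4/18 (22 percentage points) is:
- 18 women among 36: 0.244.
- 12 or 24 women among 36: 0.197.

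**Age, given an 18:18 split.** The standardised mean difference has standard error √(2/18) = 0.333. P(|difference| > 0.5 SD) = 2 × [1 − Φ(0.5/0.333)] = 2 × [1 − Φ(1.5)] = 0.134. If ages were uniform over 60–75, the SD would be 15/√12 = 4.33 years, so 0.5 SD is about 2.2 years.

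**A different reading of the rule.** Suppose the distinct numbers 1 to 36 were handed out in random order. Eighteen are odd and eighteen even, so 18:18 is certain. The gender calculation becomes hypergeometric: a gap of at least 4 women between arms has probability 0.318 with 18 women and 0.289 with 12 or 24. The age figure stays at 0.134. On this reading the size promise is met, but the matching promise is still not secured.

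**The case against.** The strongest reply is that nothing invalid is described. Allocation is random and the sequence comes from someone outside the study. Simple randomisation is a valid method at this size, and the balance wording may mean only an equal allocation ratio. All of that stands. On the ratio reading, however, the fixed 18 per group and the matching sentence remain unsupported.

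A reader might infer more than the documents support, in four ways.

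- **That the stated rule cannot give balanced or matched groups, or that they could be reached only by interfering after the draw.** Neither is so. An 18:18 split can arise by chance. Stratifying or pairing people before the draw would also satisfy the promise legitimately. The defect is that no such step is written and the rule that is written does not include one.
- **That a chance age or gender difference would bias the comparison.** It would not. Under valid randomisation, chance imbalance is random error already allowed for in the test's error rate.
- **That people will be swapped or the list redrawn.** No part of the protocol says so. This harm is conditional on conduct that is not described.
- **That age imbalance would weigh heavily on the result.** The Introduction says competing-noise effects grow with age, but it mainly contrasts old with young and gives no gradient within 60–75. The sample-size variable is change from before to after training, so stable age differences in level largely cancel. The protocol also plans to use age-related normative equations when assessing improvement.

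**Conclusion.** The point holds as an inconsistency between a stated rule and stated results. On the natural reading, the odd/even rule misses the planned 18:18 split in 87% of allocations (1 − 0.132), gives 22:14 or worse in 24%, and leaves a gender-share gap of at least 22 points in about 20–24%. Given 18:18, a mean age gap above 0.5 SD has a 13% chance.

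These figures rest on 36 participants, independent assignment with probability 1/2, 12 to 24 women among the 36, and a normal approximation for mean age. Unequal size costs little power, and chance imbalance costs precision only. The weight of the point lies in an unexplained matching promise at a stage when participants' ages and genders can already be known. It should be fixed before allocation. It does not show that the trial's randomisation is invalid as written.

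**What to change.** Replace the odd/even rule with restricted randomisation stratified by gender and age band. The sponsor should choose and record the age cut-point before the draw. The same independent staff member then draws half of each stratum at random to each arm.

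A stratum with an odd count will differ by one between arms, so with four strata the arms could differ by up to four. Because 36 is even, the number of odd-sized strata is also even. Giving the extra person to intervention in a randomly chosen half of those strata, and to control in the rest, restores exactly 18:18.

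In the text, say that the groups are stratified by age and gender, in place of saying they are matched. Include the stratification factors in the Part 2 analysis model.

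If simple randomisation is kept, remove the matching sentence and the fixed 18 per group, and state the total of 36 with an equal allocation ratio.

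The cost is one new allocation list, a sentence or two of protocol text and slightly more analysis work, with no added participants or staff. Once allocation has taken place, the design part of this remedy is no longer available.

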^30^. We will develop similar equations, compare them with the published equations, and will use these normative functions to assess improvements in performance after training.

In this step of the research, construct validity will be used to determine the validity of the test. For this purpose, Speech, Spatial, and Qualities of Hearing Scale (SSQ) questionnaire score of each individual will be compared against the informational masking score
^31^.
Figure S1 (Extended data) represents the participant’s timeline of the first part of the study.

***Part 2: the effect of auditory spatial training on the informational masking release.*** This part of research will be conducted in three steps: before auditory spatial training, during training, and after training.

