**2. Providing auditory spatial training (intervention group only)**

Auditory spatial training is designed based on five signs that are important in informational masking release: angular differentiation between target and competing signals
^16,
34–
36^; signal to noise ratio
^34^; similarity and difference between the target and competing signals
^12^; similar or different gender for target and competing signals
^12,
37^; and meaningfulness of the competing signal
^12^. As one of the main principles of any auditory training program is progression in difficulty so the training sessions will be divided into three general steps by considering the competing signals. In the first step, meaningless competing signals will be used like white noise. In the second step, in order to make the training process somewhat difficult, meaning-carrying signals like speech babble consisting of four speakers will be used. Finally, for making more difficulty, sentence materials with male and female genders will be used. The reason for using the gender factor is that consideration of gender similarity or difference between target and competing signals is one of the signs that adults use for informational masking release
^12,
37^.

In all steps, the target signal will be presented from the loudspeaker at 0-azimuth degree and competing signals from different azimuth angles such as ±45, ±90 and 0
^38,
39^. Therefore, the difficulty of training will grow in each step by reducing the azimuth angle of the competing signal
^40^.

Sentence signals are selected from Persian version of QuickSIN
^41^. Every step of training is implemented as follows:

The intensity of the competing signal is fixed at 60 dBSPL, and at the beginning the intensity of target signals is 70 dBSPL. Three first sentences will be used for familiarization. If an individual needs more practice, more familiarization sentences will be provided.

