An individual will be requested to identify the keywords heard in the target sentences. In the case of true and false identification, required feedback will be provided. If the individual identifies more than 50% of the keywords, the sentence will be considered true. In this signal to noise ratio, 5 sentences will be provided where if the individual identifies more than 50% of the presented sentences, the signal to noise ratio decreases in 5dB steps, after which 5 sentences will be provided again for the individual. If the individual does not have the capability to correctly identify more than 50% of the presented sentences in each signal to noise ratio, the training begins where this signal to noise ratio will be considered as the initial level. The training will continue for 20 minutes and the intensity will change in an adaptive procedure, such that in the case of correct identification of a sentence, the intensity will be decreased by 1.5dB while it will be increased by 2.5 dB if the individual scored less than 50% of words correctly. At each intensity where an individual can correctly identify the sentences, the next sentence will be presented and the above process will repeat.

The optimal condition for perceptual auditory learning includes active listening to high repetition of signals during the consecutive educational sessions, which is conducted within a short time interval. Since long-term training is not a very suitable option in the clinic
^2^, trainings will be repeated three times a week completed in 5-week cycles
^42^.

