### Data analysis

Central tendency and dispersion indices (mean and standard deviation) will be used in descriptive analysis of data. In data analysis and for determining the reliability of the Persian version of the coordinate response measure (CRM) corpus, paired t-test and Pearson correlation will be used in the case of normality of data; otherwise, Spearman test will be employed, and one-way ANOVA will be utilized for determining intra-class correlation coefficient.

In part 2 of the research, repeated measures ANOVA values will be used for inter-group comparisons and two-way ANOVA will be employed for comparison among groups. SPSS software (V20.0, IBM Corporation, New York, USA) will be used for statistical data analysis and the significance level for all tests will be 0.05.

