### Ethical statement and consent to participate

The Medical Ethics Committee of Iran University of medical sciences approved the study protocol (IR.IUMS.REC.1397.303) and the ethical principles of the ethics committee will be observed in this research. Researchers will send any amendments to the protocol in the future to the ethics committee.

One of the researchers of this study will obtain written informed consent from patients willing to participate in the trial (see Extended data). The purpose of the research and its steps will be explained for all participants before the study start. Confidentiality of data and results of tests will be ensured to participants. Participants will be made aware that they can refrain from cooperation in the study when they want. Conducting tests has no side-effects for the studied individuals and all tests and training sessions will be without cost to the participants.

Since this will be the first time of performing this training, we will running a focus group and asking our participants what they will think of the intervention and how likely they will continue performing the auditory training in the future.

To promote participant retention and complete follow-up, in every training session the examiner will provide feedback to all participants and will inform them about the training progress. The researcher will ask them about the impact of training on the participant’s daily communication conversations. Also at the first of each training session the initial level of training will be calculated and if there will be a progress in the initial signal to noise ratio which train will be started from that, the examiner will inform the patient.

All data will be entered into forms which are prepared for data collection (see
Table S2; Extended data) and the participant files will be stored at study site and will be maintained in a secure place and manner. Participant files will be maintained in storage for a period of 2 years after completion of the study. Only Principal Investigators will be given access to the study data.

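### The exclusion criterion on unwillingness can be applied after allocation and, together with complete-case repeated measures ANOVA, can turn the Part 2 comparison into one of completers only

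*Protocol article*

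**What the plan says.** Under *Study design, setting and participants*, the exclusion criteria apply to everyone in both parts of the study and read "unwillingness for participation in each step of research and not meeting inclusion criteria". Under *Study procedures*, Part 2 is introduced with the same word: "This part of research will be conducted in three steps: before auditory spatial training, during training, and after training".

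The abstract gives the training load: "Intervention: 15 sessions of auditory spatial training". The training section adds that "trainings will be repeated three times a week completed in 5-week cycles", and its heading restricts training to the intervention group. Controls receive no rehabilitation. Both groups are assessed before training, immediately after it and five weeks later.

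The consent section tells participants that "they can refrain from cooperation in the study when they want". The sample size section allows for loss: "By assuming 20% drop out, so we will use 18 people in each group". For Part 2, *Data analysis* states that "repeated measures ANOVA values will be used for inter-group comparisons", with two-way ANOVA alongside.

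**The concern.** An exclusion criterion that refers to every step, in a study part whose steps run past allocation, can be used to remove a person after randomisation. Unwillingness about the training sessions can arise only in the intervention arm, because only that arm has them. If people who gain little are more likely to stop, the trained group keeps its better responders and the effect is overstated.

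The named analysis pushes the same way. Repeated measures ANOVA in its usual form needs a complete set of visits per person, so a participant who misses one of the three assessments drops out of the model altogether.

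These are two separate routes to a completers-only comparison. Changing the model alone would not close the first, because a person removed under an eligibility rule never reaches the model.

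**Working it through.** **1. Does the wording reach past allocation?** The criterion covers each step. *Study procedures* names three steps for Part 2: before, during and after training. The second and third follow allocation, so on the article's own use of the word the rule can apply to a randomised person. Against this, the list of assessments before training includes taking a history to confirm the inclusion and exclusion criteria, which suggests a check at entry. Both readings are open.

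**2. Does the burden differ by arm?** Three sessions a week for five weeks is 3 × 5 = 15, which agrees with the abstract. Controls have 0 sessions. Both arms have the same assessment visits.

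**3. The planned loss.** 14 / (1 − 0.20) = 17.5, rounded up to 18, so the dropout step reproduces. The plan therefore expects about 14 of 18 per arm to contribute data. The 14 itself does not follow from the stated inputs: with the difference squared in the denominator, 7.849 × (25.17² + 18.15²) / 12.33² = 49.7. That is a separate matter and is not used here.

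**4. How large could a bias be?**

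From the sample size section: SD of improvement 25.17 (intervention) and 18.15 (control); planned difference 37.5 − 25.17 = 12.33; 18 per arm.

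Assumed, and not in the documents: the number lost in each arm, and the correlation r between staying and a good response.

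If the k people of 18 ranked lowest on a normal variable correlated r with response are removed, the mean of those who remain shifts up by r × SD × φ(z)/(1 − q), where q = k/18 and z is the q-quantile of the standard normal.

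- k = 4: q = 0.222, z = −0.765, φ(z)/(1 − q) = 0.383
- k = 2: q = 0.111, z = −1.221, φ(z)/(1 − q) = 0.213

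Bias = r × (25.17 × intervention factor − 18.15 × control factor):

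| Lost (intervention v control) | r = 0 | r = 0.3 | r = 0.5 |
|---|---|---|---|
| 4 v 0 | 0 | 2.9 | 4.8 |
| 4 v 2 | 0 | 1.7 | 2.9 |
| 4 v 4 | 0 | 0.8 | 1.3 |

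For example, 4 v 0 at r = 0.3 is 0.3 × 25.17 × 0.383 = 2.9, and 4 v 4 at r = 0.5 is 0.5 × 0.383 × (25.17 − 18.15) = 1.3.

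Simulation (40,000 trials per setting, no true effect, 18 per arm before loss) gives slightly smaller values, as expected with finite groups: 2.8 and 4.6 for 4 v 0, 1.7 and 2.8 for 4 v 2, and 0.8 and 1.3 for 4 v 4. Against 12.33, the 4 v 0 values are about 22% to 39% (2.7/12.33 to 4.8/12.33, the lowest simulated value across repeated runs to the highest from the formula). The limiting case r = 1 with 4 v 0, where the four worst responders leave, gives 9.1 to 9.6 points.

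**5. False-positive rate in the same simulation.** A pooled t-test on change at 5% rejects in 7.6% (r = 0.3) and 10.6% (r = 0.5) of trials for 4 v 0, and in about 5.5% and 6.1% for 4 v 4. With 4 v 0 and random loss it already rejects in 6.0%, because group sizes and SDs are unequal; Welch's test gives 5.0% there. About one point of the excess is therefore not due to selective loss. The t-test stands in for the planned ANOVA.

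**The case against.** The strongest reply is that this is an ordinary screening rule: do not enrol someone unwilling to complete every step. It sits in the eligibility paragraph, is joined to failure of the inclusion criteria, and covers Part 1, which is cross-sectional and not randomised. The criteria are confirmed at the preliminary interview, and the training and post-training sections never apply them again. A reader might infer that randomised people who stop attending are in fact excluded and that the plan is completers-only. The article does not say so, and that reading goes too far.

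The other passages do not establish it either. The right to stop is a normal consent provision. The 20% allowance is routine and is the same for both groups. The article also plans measures to promote retention and complete follow-up, although these consist of feedback at training sessions, which controls do not attend.

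A reader might also take the 22% to 39% as the expected bias. It rests on a 4 v 0 loss, whereas the plan assumes the same dropout in each arm, and controls who receive nothing may leave too. No correlation or arm-specific dropout rate appears in the documents. Stopping training is also not the same as refusing assessment: the rule does harm only to people who stop training but would still come to be tested, and their number is unknown.

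Finally, analysis populations and missing-data rules are commonly left to an analysis plan that is not shown, so their absence is no finding. What stands is what the article does state: a criterion worded so that it can act after allocation, and a named analysis that usually discards incomplete cases. An analysis plan that kept everyone as randomised would still conflict with the first under its wider reading.

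**Conclusion.** The concern holds as a defect of wording and of the stated analysis, not as proof that leavers will be excluded. The criterion can be applied after allocation, one arm alone carries the 15 sessions, and repeated measures ANOVA in its usual form also loses anyone with a missing visit. The comparison can therefore become completers-only.

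The size is conditional on assumptions from outside the documents: about 3 to 5 points against 12.33 with 4 of 18 lost from the intervention arm only and a correlation of 0.3 to 0.5 with poor response; about 1 point with equal loss in both arms; zero if loss is unrelated to response. It is worth correcting because the two readings give different analysed groups, and that choice should not be made once allocation is known.

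**What to change.** - In the eligibility section, limit the criterion to unwillingness expressed before allocation, and state that nobody is excluded under it afterwards.
- Invite every randomised participant to both post-training assessments, whatever their training attendance, unless they withdraw consent.
- In *Data analysis*, replace complete-case repeated measures ANOVA with a likelihood-based mixed model for the three visits, by allocated group, using all available visits. A completers analysis may be kept as a sensitivity check.

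This removes exclusion by rule and loss of whole participants for one missed visit. It does not correct dropout that depends on unobserved outcomes, and someone who attends only at baseline adds little to the estimated effect, so keeping people in assessment still matters.

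The cost is small: a few sentences, a little more analysis work, and possibly a slightly less favourable estimate. No additional participants or scheduled visits are needed. According to *Study status*, enrolment had been done but allocation had not, so at the time of the article the change could still be made before anyone's group was known.
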